#### 2.3.4. Outcomes

Primary outcome:

The primary outcome is the overall efficiency rate of treating objectives including PP-NRS, EASI, SCORAD, POEM, and DLQI at 12 weeks after treatment, which is calculated as “Total number of participants with effective treatment of 5 treating objectives/total number of participants *100%”. Criteria for effective treatment are as below: ① PP-NRS absolute score ≤ 4; ② EASI-50, EASI-75, or EASI ≤ 7; ③ SCORAD-50, SCORAD-75, or SCORAD ≤ 24; ④ POEM absolute score ≤ 7; ⑤ DLQI absolute score ≤ 5.

Secondary outcomes:The respective efficiency rate of PP-NRS, EASI, SCORAD, POEM, and DLQI, which is calculated as “Total number of participants with effective treatment of PP-NRS, or EASI, or SCORAD, or POEM, or DLQI/total number of participants *100%”;The economic consumption such as the travel expenses, expenses with lost working days, accommodation expenses, medical expenses, etc.;Satisfaction evaluation, defined as the assessment for the overall medical services by answering questions about their level of satisfaction with healthcare: 0 means completely dissatisfied, and 100 means very satisfied, and the participants or their guardians give a score between 0 and 100.

#### 2.3.5. Sample Size Calculation

Based on our preliminary investigative results, we estimate that the overall efficiency rate is 35% (unpublished data), and we hypothesize that the overall efficiency rate increases to 55%, which is clinically significant, after the implementation of the app. Assuming the difference between the two groups was a 5% significance level and a power of 0.80, 96 participants in each group are required. Considering an estimated 20% dropout rate, 116 participants in each group and a total of 232 participants are required in this trial.

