#### 2.3.7. Statistical Analysis

Spss29.0 software will be used to analyze the data according to the principle of intent to treat. Demographic data are described by mean, standard deviation, frequency, median, percentage, etc. All data are tested for normal distribution, the *t*-test is used for continuous variables that conform to normal distribution, the chi-squared test is used for classified variables, and a nonparametric test is used for variables that do not conform to normal distribution. After 2, 4, 8, and 12 weeks of treatment, the sub item compliance rates of PP-NRS, EASI, SCORAD, POEM, and DLQI are analyzed by repeated measures of variance. *p* < 0.05 means that the difference is statistically significant.

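### The stated 116 per arm does not cover the stated 20% dropout: keeping 96 evaluable needs 96/0.80 = 120, so power at 20% dropout is about 79%, not 80%

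*Protocol article*

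**What the plan says.** Section 2.3.5 (Sample Size Calculation) of the protocol article gives every input. For the comparison rate: "we estimate that the overall efficiency rate is 35% (unpublished data"). The app is assumed to raise this to 55%. The error rates are "a 5% significance level and a power of 0.80", with no statement of one or two sides. From these the section concludes that "96 participants in each group are required", and then: "Considering an estimated 20% dropout rate, 116 participants in each group and a total of 232 participants are required in this trial". The abstract repeats the total of 232.

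Two other places bear on who is counted. Section 2.3.4 (Outcomes) defines the primary outcome as "Total number of participants with effective treatment of 5 treating objectives/total number of participants", expressed as a percentage. Section 2.3.7 (Statistical Analysis) says the software will be used to "analyze the data according to the principle of intent to treat". Neither says how a participant who drops out before week 12 is counted. Section 2.3.5 does not say whether the 35% and 55% are rates among those assessed or among all enrolled.

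**The concern.** A dropout rate is a fraction of those enrolled. To end with 96 after losing 20%, the 96 must be divided by 0.80, not multiplied by 1.20. The stated 116 fits the multiplication and not the division. If so, the required number, the dropout allowance and the inflated number cannot all be true together, and the 80% power is not what the trial has at its own assumed dropout.

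At stake is the accuracy of a basic design statement. The 96 carries no reserve, since it is the smallest whole number that reaches 80%. Any shortfall in evaluable participants therefore takes power below the stated value.

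**Working it through.** **Inputs** (all from section 2.3.5): p1 = 0.35, p2 = 0.55, difference 0.20, alpha 0.05, power 0.80, 96 per arm before inflation, dropout 20%, 116 per arm after. Two-sided testing is assumed because it reproduces the 96; a one-sided test would need 76.

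**1. Reproduce the 96.** Pooled-variance formula, with p̄ = 0.45:

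n = [1.960 × √(2 × 0.45 × 0.55) + 0.842 × √(0.35 × 0.65 + 0.55 × 0.45)]² / 0.20²

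= [1.960 × √0.495 + 0.842 × √0.475]² / 0.04 = 95.94, so 96 per arm. This agrees with the article.

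**2. Apply the 20% dropout.**
- Division: 96 / (1 − 0.20) = 120 per arm, 240 in total.
- Multiplication: 96 × 1.20 = 115.2, rounded up to 116 per arm, 232 in total. This is the stated figure.

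Other usual starting points do not lead to 116 by division. The unpooled n of 93.2 gives 117 (118 if first rounded up to 94), and the continuity-corrected n of 106 gives 133.

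**3. What 116 leaves.** 116 × 0.80 = 92.8 per arm, about 3 short of 96. The largest dropout at which 96 remain is 1 − 96/116 = 17.2%.

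**4. Power at that number, dropouts excluded.** Normal approximation:

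power = Φ[(0.20 × √n − 1.960 × √0.495) / √0.475]

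| Evaluable per arm | Normal approximation | Exact, chi-squared test |
|---|---|---|
| 96 | 80.0% | 80.1% |
| 93 | 78.7% | 78.1% |
| 92.8 | 78.7% | – |
| 92 | 78.3% | 77.4% |

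The loss is about 1.3 points at 92.8 by the approximation, and 2.0 to 2.7 points by exact calculation at 93 or 92.

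**5. Range if dropouts are not excluded (assumptions, not statements of the plan).** Same formula, 116 per arm all analysed:
- *35% and 55% are rates among those assessed; 20% drop out in each arm and count as not effective.* Expected rates become 0.80 × 0.35 = 28% and 0.80 × 0.55 = 44%. Power is 72.1% (73.6% at 120 per arm).
- *35% and 55% already apply to all enrolled.* Rates stay at 35% and 55%. Power is 87.0%.

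**The case against.** The strongest reply is that the slip hardly matters. It amounts to 4 participants per arm, or 3.4% of 116, and between one and three points of power. The uncertainty in the assumed rates is worth more: with 96 per arm, 35% against 54% already gives only 75.9%. No estimate, test or participant is affected. That reply stands as to size and is why this is a minor point. It does not reconcile the figures, because 116 × 0.80 is not 96.

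It can also be said that the article shows no inflation formula, so the multiplication by 1.2 is a guess about how 116 arose. That is fair, and it is labelled as inference here. The inconsistency does not depend on it.

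A reader might go further and infer a material loss of power: the outcome is divided by all participants and the analysis is by intention to treat, so dropouts must count as failures and the trial has only about 72% power. The article does not support this. Its denominator is described as participants, without the word randomised, and naming the intention-to-treat principle does not say that a missing week-12 result counts as not effective. The source of the 35% is unpublished and its population is not described. The handling of missing outcomes is commonly left to the analysis plan or full protocol, which are not at hand, so its absence is no fault. The 72% is one end of a range whose other end is about 87%.

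**Conclusion.** The point holds as an arithmetic inconsistency in section 2.3.5. A requirement of 96 per arm with 20% dropout leads to 120 per arm (240 in total), not 116 (232). With 116 and 20% dropout, about 93 per arm remain and power is about 78.7%, or about 78% by exact calculation. The stated 80% holds only up to 17.2% dropout. This rests on a two-sided test and on dropouts leaving the analysis, which is what an inflation for dropout presupposes.

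The severity is minor. The span of about 72% to 87% in step 5 is conditional on assumptions that the article neither makes nor excludes. It is no evidence that the trial is materially underpowered, but it does show why the population behind the 35% and 55% should be named.

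**What to change.** Restate the end of section 2.3.5 without enrolling more, for example: *116 participants per arm (232 in total) retain 96 evaluable participants per arm and 80% power with dropout of up to about 17%; at 20% dropout with dropouts excluded, power is about 79%.* Add that the test is two-sided, if it is, and one sentence saying whether the 35% and 55% describe participants assessed at week 12 or all participants enrolled.

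The cost is a change of wording and a slightly less favourable stated power; the total of 232 in the abstract can stay. If the sponsor prefers to keep both 20% dropout and 80% power with dropouts excluded, the figures are 120 per arm and 240 in total, which is 8 more participants.

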#### 2.3.6. Study Timeline

The study timeline is illustrated in Figure 4, which outlines the key milestones and phases of the study, from patient recruitment to data analysis.

#### 2.3.7. Statistical Analysis

Spss29.0 software will be used to analyze the data according to the principle of intent to treat. Demographic data are described by mean, standard deviation, frequency, median, percentage, etc. All data are tested for normal distribution, the *t*-test is used for continuous variables that conform to normal distribution, the chi-squared test is used for classified variables, and a nonparametric test is used for variables that do not conform to normal distribution. After 2, 4, 8, and 12 weeks of treatment, the sub item compliance rates of PP-NRS, EASI, SCORAD, POEM, and DLQI are analyzed by repeated measures of variance. *p* < 0.05 means that the difference is statistically significant.

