The “Data management” function is designed for medical staff to manage the patients more conveniently and design the medical research. They can log in to the app platform website to collect and export data and carry out statistical analysis and big data mining. The app itself can also do simple statistics and management of data. For example, data such as EASI, POEM, and PP-NRS scores at the time points of before treatment, 2 weeks, 4 weeks, 12 weeks, and 6 months after treatment could be automatically generated into statistical reports to be presented in the form of histograms or curves. The app can also be further improved and updated to the new version through the analysis of users’ habits, and the function modules could be optimized with the high frequency of use and the feedback from both medical staff and patients.

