#### 2.3.1. Participants

Inclusion criteria: patients diagnosed with moderate to severe AD, aged 2–75 years; be able to communicate in Chinese; with basic reading and writing skills; participants or the guardian have smartphones or pads and are familiar with use skills.

Exclusion criteria: mental illness; personality disorder; language barrier; hearing impairment; communication difficulties; with serious coexisting diseases, such as cardiopulmonary insufficiency, liver dysfunction, renal dysfunction, blood system diseases, tumors, or other diseases; other situations that are not suitable for participating in the clinical trial.

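### The primary comparison is a chi-squared test with no covariate: valid and consistent with the sample size, but adjusting for baseline EASI and age would add power and protection against chance imbalance at no data cost

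*Protocol article*

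**What the plan says.** Section 2.3.7 chooses tests by variable type. For categorical data the rule is "the chi-squared test is used for classified variables". The only other method there that touches response rates is a repeated-measures analysis, which is confined to the five separate component rates at weeks 2 to 12.

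Section 2.3.4 defines the primary outcome as the proportion of participants who meet all five criteria at 12 weeks. PP-NRS, POEM and DLQI are judged by an absolute score alone. EASI and SCORAD can be met either by an improvement criterion (50 or 75) or by an absolute score.

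Section 2.3.1 admits "patients diagnosed with moderate to severe AD, aged 2–75 years". Section 2.3.2 describes a computer-generated allocation and names no stratification factor.

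Section 2.3.5 plans on a control rate of 35% ("we estimate that the overall efficiency rate is 35% (unpublished data") and a rate of 55% with the app, and concludes that "96 participants in each group are required". Neither this section nor 2.3.7 mentions a covariate.

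**The concern.** The composite is likely to depend on where a participant starts. Three of its five criteria are fixed cut-offs, all five must be met, and a participant who starts close to a cut-off has less distance to cover. Eligibility is wide in both age and severity, so starting points will differ.

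A test with no covariate treats all of that variation as noise. It also leaves the estimated difference exposed to any chance imbalance in severity or age. If baseline severity is prognostic, a prespecified adjusted analysis gives a more powerful test from the same participants. Prespecification matters here because the trial is open-label: if severity turned out unbalanced, an adjustment chosen afterwards would be hard to defend.

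**Working it through.** **1. Which test applies to the primary outcome.** The outcome is binary at one time point (2.3.4). The variable-type rule in 2.3.7 offers only the chi-squared test for such a variable. The link is by inference, since 2.3.7 does not name the primary outcome, but the sample size supports it (step 2).

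**2. Reproducing the plan's figure.** Inputs from 2.3.5: 35% and 55% (mean 45%, difference 0.20), 5% significance, 80% power. Sidedness is not stated; two-sided reproduces the figure.

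n per group = [1.960·√(2·0.45·0.55) + 0.8416·√(0.35·0.65 + 0.55·0.45)]² / 0.20²

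= [1.960·0.7036 + 0.8416·0.6892]² / 0.04 = (1.379 + 0.580)² / 0.04 = 95.9, rounded up to **96**.

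This equals the stated 96 per group (power 80.0%). The plan is sized for an unadjusted two-proportion test, so design and analysis agree.

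**3. Which baseline data must exist.** In their conventional meaning, EASI-50/75 and SCORAD-50/75 are percentage improvements from baseline, so they cannot be scored without baseline EASI and SCORAD in both arms. Age is checked at eligibility. PP-NRS, POEM and DLQI are scored as absolute values at 12 weeks and need no baseline. Section 2.2 mentions "EASI, POEM, and PP-NRS scores at the time points of before treatment", but only as an example of the app's automatic reports, so it does not show that those questionnaires are collected before treatment in controls.

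**4. Gain from adjustment, by approximation.** Let R² be the share of outcome variance explained by baseline. The documents give no value, so it is an assumption shown over a range. The effective size is 96/(1 − R²), and power = Φ{[0.20·√n − 1.379]/0.6892}.

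- R² = 0: n = 96, power 80.0%
- R² = 0.05: 96/0.95 = 101.1, power 82.0%
- R² = 0.10: 96/0.90 = 106.7, power 84.0%
- R² = 0.20: 96/0.80 = 120, power 88.1%

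**5. Gain by simulation.** 96 per group, 8,000 trials per row, marginal rates held at 35% and 55%. The chi-squared test is compared with the arm coefficient in a logistic model with one standardised baseline covariate.

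| Log-odds ratio per SD (assumed) | R² | Chi-squared | Adjusted | Gain (points) |
|---|---|---|---|---|
| 0 | 0 | 80.6% | 80.4% | −0.2 |
| 0.3 | 0.02 | 80.7% | 81.1% | 0.3 |
| 0.5 | 0.05 | 79.9% | 81.9% | 2.0 |
| 0.8 | 0.12 | 79.3% | 84.1% | 4.8 |
| 1.0 | 0.17 | 80.1% | 86.6% | 6.5 |
| 1.2 | 0.22 | 79.8% | 88.3% | 8.5 |

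Each power has a Monte Carlo standard error of about √(0.8·0.2/8000) = 0.4 points, so the first two rows show no real difference. A log-odds ratio of 1.1 lies between the last two rows, at 7 to 8 points. A further simulation with two covariates, one of them pure noise, also showed no loss of power when prognosis was nil, and gains of about 2 to 8 points for log-odds ratios of 0.5 to 1.1.

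**6. Type I error.** Under no effect (1,000 trials per scenario, 93 per group), the adjusted test rejected in 5.0% to 5.9% of trials and the chi-squared test in 5.0% to 6.7%. The Monte Carlo standard error is about √(0.05·0.95/1000) = 0.7 points. Apart from the upper chi-squared figure, which lies a little over two standard errors above 5%, these are within ordinary simulation noise.

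**7. If all enrolled are analysed.** At 116 per group, with the same rates assumed, the simulated gains are smaller: 88.2% against 87.5% at 0.5, 90.6% against 87.3% at 0.8, and 93.6% against 87.9% at 1.2.

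**The case against.** The strongest reply is that nothing here is wrong. The chi-squared test is valid in a randomised trial, its error rate already allows for chance imbalance, and it is the test the sample size was built on. That stands in full, and the point is put as an improvement only.

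A second reply is that the article condenses a fuller plan that may name covariates. This carries less weight: the article does state a method for binary outcomes, and the sample size is that of the same unadjusted test. It does stand for stratification. The article's silence does not show that randomisation is unstratified, and the point does not depend on it.

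Third, the cut-off argument applies most directly to PP-NRS, POEM and DLQI, whereas EASI can be met by relative improvement. Baseline EASI may therefore be a weaker predictor than the questionnaire scores. That also stands. EASI is proposed because the endpoint guarantees that it exists in both arms.

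Two stronger readings are tempting and are not supported:

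- A reader might infer that adjustment is needed to repair an underpowered trial, since 116 less 20% leaves about 93 per group and a chi-squared power of 78.7%. That shortfall comes from how dropout was added (96 × 1.2, against 96/0.8 = 120) and is a separate matter. It also assumes that dropouts are excluded, while 2.3.7 declares intention to treat and the denominator in 2.3.4 is all participants.
- A reader might infer that every component's baseline score is needed for the endpoint and therefore available. Only EASI and SCORAD are.

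**Conclusion.** The point holds as a free gain in efficiency and in protection against chance imbalance, not as an error. At 96 per group the gain is close to nil if baseline is barely prognostic, and about 2, 4 to 5, and 7 to 8 points of power at log-odds ratios of 0.5, 0.8 and 1.1 per SD, with type I error near 5%.

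It rests on four assumptions:

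- The chi-squared rule governs the primary outcome. This is inferred, and the sample size supports it.
- Baseline EASI is recorded in both arms. This is inferred from the endpoint definition; no baseline visit is stated in so many words.
- The prognostic strengths are assumed, because the documents give none. The direction is plausible; the size cannot be fixed from the text.
- The tabulated power is for the arm coefficient in the logistic model. The standardised difference recommended below was not itself simulated.

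**What to change.** In 2.3.7, name the primary analysis explicitly: logistic regression of the 12-week composite on arm, baseline EASI (continuous) and age, with the form of age fixed in advance. Add baseline PP-NRS, POEM or DLQI only if they are collected before treatment in both arms.

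Report the covariate-standardised difference in response rates with a 95% confidence interval. The target then remains the 20-point marginal difference on which 2.3.5 is based; the logistic odds ratio is conditional and not collapsible, so it should not be the headline estimate. Keep the chi-squared test as a sensitivity analysis.

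The cost is wording only, with no additional participants, visits or measurements. The 96 per group can stay, since it is the size for the less efficient test. The change must be fixed before any outcome data are seen by arm.

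### The five yes/no target results at weeks 2 to 12 are assigned to repeated-measures ANOVA, which in its classical form keeps only complete cases and tests an average over visits rather than week 12

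*Protocol article*

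**What the plan says.** All references are to the protocol article.

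- **Outcome (2.3.4).** A secondary outcome is "The respective efficiency rate of PP-NRS, EASI, SCORAD, POEM, and DLQI": participants who meet the criterion, divided by all participants. The criteria are thresholds, for example "PP-NRS absolute score ≤ 4".
- **Repeated analysis (2.3.7).** The plan is that "the sub item compliance rates of PP-NRS, EASI, SCORAD, POEM, and DLQI are analyzed by repeated measures of variance". The visits named for this are weeks 2, 4, 8 and 12. I read this as repeated-measures analysis of variance, and the sub-item rates as those of 2.3.4.
- **General rules (2.3.7).** For categorical data, "the chi-squared test is used for classified variables". Continuous data get a t-test if normal; otherwise "a nonparametric test is used for variables that do not conform to normal distribution".
- **Principle (2.3.7).** The trial will "analyze the data according to the principle of intent to treat".
- **Visits (2.3.3).** App-group visits are fixed in advance. The treating dermatologist decides when control participants are seen.
- **Costs (2.3.4).** Another secondary outcome is "The economic consumption such as the travel expenses, expenses with lost working days, accommodation expenses, medical expenses, etc". Section 2.3.7 has no separate rule for it.

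**The concern.** Repeated-measures ANOVA is built for a continuous outcome with similar variance and correlation across visits. A yes/no outcome has variance p(1 − p), which changes as the response rate rises. The section's own rule for categorical variables does not lead to this method either.

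Three consequences matter for the five sub-item results.

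1. The classical procedure needs a value at all four visits. Deleting everyone else conflicts with intent to treat and with a denominator of all participants. The loss may differ by arm, because only app-group visits are fixed to these weeks.
2. The main group test concerns the average over four visits, whereas the trial's headline time point is week 12.
3. The arm-by-visit test works on the risk scale. If the odds ratio is constant while response rates rise, the risk differences grow, and this can be reported as an effect that changes over time.

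**Working it through.** **Inputs from the article.** Section 2.3.5 gives rates of 35% and 55%, a 5% level, power 0.80, 96 per group, 20% dropout, and 116 per group after allowance. The rates belong to the five-part primary outcome. No sub-item rates are given, so they serve here only as an illustration.

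**Assumed inputs.** The article gives no rates before week 12, no correlation between visits, no attendance and no cost spread.

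**The plan's own figure.** Two-sided pooled formula, mean rate 0.45:

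n = [1.960 × √(2 × 0.45 × 0.55) + 0.842 × √(0.35 × 0.65 + 0.55 × 0.45)]² / 0.20² = (1.379 + 0.580)² / 0.04 ≈ 96 per group.

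This agrees with the article. A week-12 comparison at 96 per group therefore has 80.0% power by formula, and 79% to 80% when simulated.

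**Does the method give wrong p-values?** Four correlated yes/no visits were simulated from a latent normal model with no difference between arms. There were 96 or 116 per arm and 5,000 runs per scenario. Rates were 5/15/25/35% with latent correlation AR(1) 0.8, AR(1) 0.9 or exchangeable 0.6. A steeper case used 1/5/15/35% with AR(1) 0.8 and 96 per arm. From 5% to 35% the variance rises from 0.05 × 0.95 = 0.0475 to 0.35 × 0.65 = 0.2275, a factor of 4.8. Even so:

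| Test | Rejections at the 5% level |
|---|---|
| Group effect | 4.9% to 5.3% |
| Arm × visit, uncorrected | 5.2% to 6.7% |
| Arm × visit, Greenhouse-Geisser | 4.1% to 5.4% |

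The 6.7% comes from the steeper case. The simulation error of one such figure is √(0.05 × 0.95 / 5,000), about 0.3 percentage points.

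**Which question is answered?** Control rates 5/15/25/35%, 96 per arm, AR(1) 0.8, 2,500 runs. Every app pattern ends at 55%.

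| App rates, weeks 2/4/8/12 | Mean difference over visits | Power, group effect | Power, arm × visit (uncorrected) | Power, week 12 |
|---|---|---|---|---|
| 5/18/35/55% (late) | (0 + 3 + 10 + 20)/4 = 8.25 points | 51% | 75% | 79% |
| 15/30/42/55% | (10 + 15 + 17 + 20)/4 = 15.5 points | 91% | 23% | 79% |
| 25/35/45/55% (constant) | 20 points | 99% | 6% | 79% |

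The week-12 difference is the same in all three rows. The group test moves from 51% to 99% with the path taken to get there.

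**Interaction scale.** 35% v 55% is an odds ratio of (0.55/0.45)/(0.35/0.65) = 2.27. Applied at every visit, it gives app rates of 10.7/28.6/43.1/55.0% and risk differences of 5.7, 13.6, 18.1 and 20.0 points. The uncorrected arm-by-visit test was significant in 47% of runs (45% with the correction).

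**Who remains with complete visits, of 116 per arm?**

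- The 20% dropout is the only loss: 116 × 0.80 = 92.8, about 93 (80%).
- 10% missing independently at each visit (assumed): 0.9⁴ = 0.656, about 76 (66%).
- 20% missing independently at each visit (assumed): 0.8⁴ = 0.410, about 48 (41%).

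**Costs, if they fail the normality test.** Simulated log-normal costs with equal arm means, 96 per arm, 2,000 runs. With log-SDs 1.2 v 0.8, a rank test rejected in 76% and the Welch test in 7%. With 1.4 v 0.7, the figures were 99% and 11%. With equal log-SDs of 1.0, both rejected in about 5%. The result thus depends wholly on the spread differing between arms.

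**The case against.** The strongest reply is that the mismatch does little harm. With about 100 per arm, averages of yes/no values behave well, and the simulations bear this out for the group effect. A reader might infer from the choice of method that the secondary p-values will be wrong. The documents and the calculations do not support that: the only inflation found is small and disappears with a standard correction. Nor can one say that the plan's intervals are wrong, since Section 2.3.7 specifies none.

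Secondly, the article does not say that incomplete participants will be dropped. Imputation before the analysis would avoid it, and rules for missing data may stand in an analysis plan that is not shown. This is fair. The conflict with intent to treat therefore attaches to the method in its classical form. The 66% and 41% figures assume independent missingness; about 80% remains if the planned dropout is the only loss. Imputation would not change the averaging or the scale.

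Thirdly, an arm-by-visit finding under a constant odds ratio is no false positive, because the risk differences really do differ. In the late-effect case that same test also has 75% power, so the effect need not be missed. Both points stand. What remains is that neither ANOVA test estimates the week-12 difference.

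Fourthly, a reader might infer that costs will be analysed by a rank test. Section 2.3.7 names neither costs nor a rank test, and Section 2.3.4 sets no aim about mean costs. A rank test is also valid for equality of distributions, and in the unequal-spread simulations the distributions do differ. The cost point is therefore only conditional.

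**Conclusion.** The point holds in a limited form. The plan assigns a method for continuous outcomes to five binary secondary outcomes, and this is a stated choice, not an omission. The consequences are possible loss of incomplete participants (20% to 59% under the patterns shown), a main test whose power varies from about 51% to 99% for one and the same week-12 difference, and an interaction test tied to the risk scale. Unequal loss between arms is plausible given the control visit schedule, but it cannot be sized from the article.

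The power and interaction figures rest on the primary outcome's 35% and 55%, together with assumed earlier rates and correlations. Actual sub-item rates should be higher, since the primary outcome requires all five criteria at once. The error rates apply to complete data.

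The primary outcome at week 12 is untouched, and a sub-item rate at a single visit is still covered by the chi-squared rule. This is worth correcting, but it does not threaten the trial's main result.

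**What to change.** In Section 2.3.7, replace the repeated-measures ANOVA with a logistic GEE or a mixed-effects logistic model for each sub-item. Include arm, visit, arm × visit and the baseline score, and use all available visits. Report the risk difference with 95% CI at each visit, with week 12 as the main one; from a mixed model this needs averaging of predicted probabilities over participants.

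Using all visits does not make missing data harmless. A standard GEE makes a stronger assumption about why visits are missing than a mixed model does. Neither model can supply control-arm data at weeks when nobody was seen, so the text should also say how control visits are matched to the four weeks.

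For costs, if a statement about mean cost is intended, report the difference in arithmetic means with a bootstrap or Welch 95% CI, without a normality pre-test. With very skewed costs and unequal spread the Welch test rejected in up to 11% of simulated trials, so the bootstrap interval is worth reporting beside it.

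The cost is a change of wording and slightly more analysis work. Sample size and visits stay as they are.
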